#### Self-reported work-specific characteristics

Work-specific characteristics will be measured by the Experience and Evaluation of Work 2.0 (QEEW2.0) questionnaire [91]. For the purpose of this study, we selected ten subscales: (1) Pace and amount of work, (2) Emotional workload, (3) Mental workload, (4) Physical effort, (5) Relationship with supervisor, (6) Relationship with colleagues, (7) Work pleasure, (8) Career opportunities, (9) Organizational commitment, and (10) Changing jobs (intention to change jobs). These scales will be rated on a 4-point Likert scale ranging from always to never (subscales 1–6), or a 5-point Likert scale ranging from strongly agree to strongly disagree (subscales 7–10). The total score of each subscale will be calculated as a measure of an individual characteristic. The QEEW2.0 is a reliable and valid measurement for research on work, wellbeing, and performance [92].

#### Surgery variables

We will register if complications (i.e. undesirable and unintended events that result from surgery) occur during and/or after the surgery (on a dichotomous scale: yes–no). This data will be monitored by the surgeon and taken from the medical record of the participant.

#### Potential influence of COVID-19

For exploratory reasons, we will examine whether results are influenced by the current COVID-19 pandemic. The participant will be requested to indicate a) to what extend there was concern about health as a result of the COVID-19 pandemic (on a numeric rating scale from 0 = *not at all* to 10 = *very much*), b) to what extent physical activity was limited due to the COVID-19 pandemic (on a numeric rating scale from 0 = *I have not at all been less physically active* to 10 = *I have very much been less physically active*), and c) if two or more of the typical COVID-19 symptoms were experienced simultaneously in the past 6 months (on a dichotomous scale: yes–no).

### Potential moderator variables

#### Self-reported intolerance of uncertainty

Intolerance of uncertainty (IU) is defined as “*the tendency of an individual to consider the possibility of a negative event occurring unacceptable, irrespective of the probability of occurrence*” [91, p. 105], which will be measured by the 12-item Intolerance of Uncertainty Scale (IUS-12) [93]. Participants are requested to indicate to what extent the statements apply to them (on a 5-point Likert scale ranging from 1 = *not at all characteristic of me* to 5 = *entirely characteristic of me)*. A total score will be calculated as a measure of responses to uncertainty. The IUS-12 has shown to be a reliable and valid questionnaire with satisfactory psychometric properties [93–96] in both clinical as non-clinical study samples [97]. IU is included as a potential moderator of the relationships between the predictors and outcome variables. In previous research, IU was found to be a potential risk factor for persistent pain, and excessive and inflexible avoidance, which both have been found to be associated with mental disorders [72, 98]. In addition, IU was found to be related to higher levels of fear and non-adaptive cognitions (e.g., worrying, ruminating, and catastrophizing) in uncertain situations, causing people who are intolerant of uncertainty to be more likely to interpret ambiguous information in a threatening way [72, 93, 98, 99]. Therefore, we assume intolerance of uncertainty to be a risk or vulnerability factor in the relation between the predictors and outcome variables of interest.

#### Self-reported optimism

Optimism is defined as “*the attitude that good things will happen and that people's wishes or aims will ultimately be fulfilled*” (American Psychological Association, n.d.). Trait optimism will be measured by the Life Orientation Test-Revised (LOT-R) questionnaire [100]. The LOT-R consists of 10 statements, on which participants are requested to indicate to what extent they agree (on a 5-point Likert scale ranging from *strongly disagree* to *strongly agree),* and has shown to have satisfactory psychometric properties [101]. A total score will be calculated as a measure of generalized optimism. Also optimism will be considered a potential moderator of the relationships between the predictors and outcome variables. Previous research has shown that optimism is related to improved psychological and physical well-being [102, 103]. It has shown that optimists typically experience less pain, better adjust to pain because of adaptive behavior, and have a better quality of life [71, 102, 104]. In addition, empirical evidence has shown that optimism is related to better outcomes after major invasive and minor elective surgeries [71]. Therefore, we assume optimism to have a protective function in the relation between the predictors and outcome variables of interest.

## Statistical analysis plan

Following an intent-to-treat approach, data from all included participants will be analyzed. Descriptive statistics will be used to explore the mean and median scores, and standard deviations of all measures. Depending on the type of dependent variable, we will apply Cox proportional-hazards regression analysis with time-dependent covariates or multiple (logistic) regression analysis, starting with a univariate analysis, followed by a multivariate analysis. If statistical power allows, interaction effect between time and all the predictor variables will also be tested to evaluate if the effect of the predictor variables is consistent in time. Additionally, we will check for site effects with the mixed model regression approach. All variables will be examined for the assumptions required for parametric analyses. Results will be evaluated at *p* < 0.05 significance level. Effect sizes (i.e., odds ratios) and post hoc power will be calculated when appropriate.

### Primary objectives

Logistic regressions will be performed to examine the effect of preoperative as well as postoperative fear of movement-related pain and avoidance behavior (and their generalization), expectancies towards recovery, expectancies towards work resumption, presence of yellow flags, on return to work at 6 weeks, 3 months, 6 months, and 12 months post-surgery. Next, a time-dependent Cox regression will be performed to examine the effect of the predictor variables on return to work over time. The same analyses will be conducted for the sustainability of work resumption at 3 months, 6 months, and 12 months post-surgery as a dependent variable.

Multiple linear regression analyses will be carried out to examine the effect of the predictor variables on the duration to resume work over time. Log-rank test and Kaplan–Meier plots will be applied to compare rates of work resumption between participants with different profiles (i.e. at work or not during the different measurement moments).

All interaction effects, including the predictor*time interactions, will be explored. Following potential confounders will be included as covariates in each analysis: age, sex, work characteristics, duration of incapacity for work, surgery complication, and the potential influence of the COVID-19 pandemic.

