## Methods

### Design

This multisite study has a prospective, longitudinal design in which individuals with radicular pain who undergo a lumbar decompression, will be followed prior to surgery up until 1 year post-surgery. Measurements take place prior to surgery (preoperative measurement), immediately after surgery (postoperative measurement), and 6 weeks, 3 months, 6 months, and 12 months post-surgery (follow-up measurements), see Fig. 1. The expected duration of the entire study is approximately 2 years.

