### Participants

Three hundred individuals with radicular pain will be recruited. Every participant will be planned for back surgery in one of the nine involved Belgian hospitals (i.e., University Hospitals Leuven, Ziekenhuis Oost-Limburg, Noorderhart Mariaziekenhuis, AZ Groeninge, GasthuisZusters Antwerp, Centre Hospitalier de Wallonie picarde, Imeldaziekenhuis, Regional Hospital Heilig Hart Tienen, and AZ Sint-Lucas Ghent). Inclusion criteria are: (a) age between 18 and 55, (b) proper mastery of the Dutch, English, and/or French language, (c) intermittent or constant invalidating lumbosciatica for less than 1 year prior to the planned surgery, operationalized by being on sick leave on the day of the surgery (documented by the surgeon), (d) radicular pain in the leg(s) due to compression, that will be treated surgically by performing a decompression without it leading to fusion and/or fixation, and (e) self-employed or has an employment contract, and is on sick leave for less than 1 year at the day of the surgery. Reasons for exclusion are (based on self-report): (a) being treated (ambulant or residential) for substance abuse, suicidal ideation, or a psychotic disorder in the year before the consult with the surgeon, (b) at least one back surgery in the last 5 years prior to the planned surgery, and (c) presence of a comorbid condition (e.g. a severe neurological deficit, a pulmonary embolism, permanent paralysis, and another pain problem in the limbs), which may affect the pain, the outcome of the surgery, the duration of the rehabilitation, and/or the participant’s capacity to return to work during the course of the study. At the end of the study, participants will receive a gift voucher worth of maximum 40 euros (at a rate of 10 euros per completed follow-up measurement).

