#### Postoperative measurement

In the week after the surgery, the predictor variables, the baseline of the outcome variables after the surgery, and the more specific work characteristics (e.g., workload, relationship with colleagues/supervisor, and pleasure in work) will be assessed. Participants will be asked to complete several self-report questionnaires to assess intolerance of uncertainty, fear of movement-related pain, avoidance behavior, expectancies towards their recovery and resumption of work, optimism, yellow flags for long-term disability and failure to return to work, pain severity, disability, quality of life, and work characteristics. The presence of unexpected complications that occurred during and/or after the surgery will be checked in the medical record of the participants. This measurement will take place during the participant’s recovery time in the hospital. The questionnaires will be implemented in REDCap and will be completed online on a laptop.

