## Measurement instruments

### Outcome variables

#### Self-reported work resumption

To measure work resumption, we make a distinction between being fit for work, work resumption, and sustainable work resumption. Being fit for work will be operationalized by not receiving disability benefits. Work resumption will be operationalized by being at work without receiving disability benefits (on a dichotomous scale), and by time to relapse. Time to relapse is defined as the duration of being at work until a participant is on sick leave again. Sustainable work resumption will be operationalized by being at work for at least three consecutive months without receiving disability benefits (on a dichotomous scale). In addition, the duration of work resumption will be measured (on a continuous scale). All these variables will be assessed using custom-made self-report questions. The custom-made questionnaires are presented in Additional file 1. In order to calculate the time to relapse and sustainable work resumption, we will ask the participants to indicate when they were incapacitated from work and when they resumed work. In addition, we will directly ask if the participant resumed work for at least three consecutive months.

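### Sustainable work resumption needs three consecutive months at work, yet it is analysed at the 3-month visit, when nobody seen on schedule can have reached it

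*Protocol article*

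**What the plan says.** Four parts of the protocol article bear on this.

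- **Outcome** (Self-reported work resumption): "Sustainable work resumption will be operationalized by being at work for at least three consecutive months without receiving disability benefits", scored yes or no. Participants give the dates on which they stopped and resumed work, and in addition "we will directly ask if the participant resumed work for at least three consecutive months".
- **Starting state** (Participants): inclusion criterion (c) is "operationalized by being on sick leave on the day of the surgery". Criterion (e) repeats the condition: the participant "is on sick leave for less than 1 year at the day of the surgery".
- **Early course** (Postoperative measurement): the first measurement after surgery falls within a week of it, during the participant's "recovery time in the hospital".
- **Analysis** (Primary objectives): return to work is analysed by logistic regression at 6 weeks, 3, 6 and 12 months. Then: "Next, a time-dependent Cox regression will be performed to examine the effect of the predictor variables on return to work over time". For the sustained outcome: "The same analyses will be conducted for the sustainability of work resumption at 3 months, 6 months, and 12 months post-surgery".

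The Design section counts all follow-up visits from surgery. The Rationale section and the abstract make sustainable work resumption the outcome of the primary objective and the primary hypothesis.

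**The concern.** The outcome is a duration that can start, at the earliest, after day 0. The visit that is meant to record its completion is set exactly that duration after day 0. Dropping the 6-week visit for this outcome suggests that the need for elapsed time was noticed, but the first retained visit is still one too early.

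Two things are at stake. A logistic regression whose outcome is all no has nothing to estimate. If a few yes answers do appear, the situation is arguably worse: the model would run, with many predictors and covariates, and would describe late form completion or reporting error under the label of the primary outcome.

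**Working it through.** The plan gives no event count or rate for this outcome, so there is no figure of its own to reproduce. Its one computed figure, the sample size for linear regression, does not bear on this point. The check is calendar arithmetic.

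**Inputs**
- Required run at work: 3 months, taken as 91 days (Self-reported work resumption).
- First possible day at work: day 1, because day 0 is sick leave (Participants).
- Visits counted from surgery: days 42, 91, 182 and 365 (Design; conversion to days is mine).
- Planned enrolment: 300 (Participants).

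**Formulas**
- Longest possible run at a visit = visit day − 1.
- Latest return day that still allows 91 days = visit day − 91.

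| Visit | Day | Longest run | Latest qualifying return |
|---|---|---|---|
| 6 weeks (not planned for this outcome) | 42 | 41 | 42 − 91 = −49: impossible |
| 3 months | 91 | 90 | 91 − 91 = 0: day of surgery, excluded by the sick-leave criterion |
| 6 months | 182 | 181 | 182 − 91 = 91 |
| 12 months | 365 | 364 | 365 − 91 = 274 |

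At the on-schedule 3-month visit the longest run is 90 days against 91 required, so the expected number of true events is 0 of 300. If the visit day itself is counted as a worked day, a return on day 1 gives exactly 91. Only a person at work the day after surgery would then qualify, at a time when the article expects participants to be recovering in hospital.

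**Late forms.** No visit window is stated. If the form is completed w days late, a qualifying return day r must satisfy 91 + w − r ≥ 91, that is r ≤ w. For an assumed w of 7, 14, 21 or 28 days, only people back at work by day 7, 14, 21 or 28 could score yes. Whether such a person counts as an event would then depend on how late the form was.

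**Cox model.** If the event is completion of the third month, the earliest event is day 1 + 91 = day 92. No event can fall before month 3.

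**The case against.** The best defence is that "The same analyses will be conducted for the sustainability of work resumption at 3 months, 6 months, and 12 months post-surgery" may mean something other than completion by the visit. It could mean being at work at month 3 in a spell that later proves to last three months, and the dates collected would allow that classification. This is a sensible outcome, but the article does not state it, and under it the 3-month status would be known only at about 3 + 3 = 6 months. What stands is that deletion is not the only remedy: a stated landmark definition would serve as well.

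Second, forms are completed at home after contact by the research assistant, so some will be late and a few very early returners could qualify. Visit windows and the exact question wording (Additional file 1, not shown) may also lie outside the article. This softens the strict zero but does not rescue the analysis. The definition, the starting state and the time point are all fixed in the article, and they conflict.

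Third, the damage is limited. The 6- and 12-month logistic regressions, the Cox model and all the return-to-work analyses can still be run. That is correct.

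A reader might go further and infer that the 12-month analysis misclassifies people who resumed after month 9 and are still at work. The document does not support this. Such a person has not completed three months, so no is the right value under the stated definition. Return to work at 12 months is analysed separately, where they count as resumed, and duration of work resumption is also measured on a continuous scale. Nothing in Primary objectives says that the Cox model would treat them as failures and not as censored. Nor does a yes at 6 months simply mean resumption by month 3: that is necessary but not sufficient, because a relapse can break the run.

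**Conclusion.** The concern holds for the 3-month time point. Under the article's own definition and inclusion criteria, an on-schedule 3-month visit has essentially no true events (0 of 300 with three months taken as 91 days and day 1 as the first possible working day). One of the three visit-level logistic regressions of the primary-objective outcome is therefore void. The conclusion does not depend on any assumed event rate. It rests on reading the outcome as a run already complete at the visit, which is the only reading written down.

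The 6- and 12-month analyses are valid. People who resumed after month 12 − 3 = 9 have not yet met the definition at month 12. That should be kept in mind when interpreting the 12-month result, but it is not an error in the plan.

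**What to change.** 1. Delete the 3-month logistic regression of sustainable work resumption and keep 6 and 12 months. Alternatively, replace it with an explicit landmark definition: at work by month 3, and later shown from the collected dates to have lasted three consecutive months. The landmark status would be close to the 6-month status, since both require a return by about day 91 and a run completed by about day 182. That overlap should be acknowledged if the landmark is chosen.
2. In the Cox model for this outcome, state that the event is dated at completion of the third consecutive month, so that no event can occur before month 3.
3. Add one sentence to the interpretation of the 12-month result, saying that those who resumed after month 9 cannot yet have met the definition.

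The cost is wording in the protocol and the analysis plan. No new data are needed, because the dates of stopping and resuming work are already collected.

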## Abstract

**Background:**

Previous studies indicated that about 20% of the individuals undergoing back surgery are unable to return to work 3 months to 1 year after surgery. The specific factors that predict individual trajectories in postoperative pain, recovery, and work resumption are largely unknown. The aim of this study is to identify modifiable predictors of work resumption after back surgery.

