### Back surgery

Over the past decades, the number of back surgeries in Belgium substantially increased. Du Bois et al. [35] reported a rise of 44% from 2001 through 2009 in Belgium. In the past decade, this increase was less pronounced and dropped to 0.44% between 2009 and 2019. From 2017 until 2019, there was even a small decrease of 1.40% [36]. Nevertheless, the number of spine surgeries is still considerable. In 2019, a total of 38,123 spine surgeries were performed. There is however no unequivocal evidence that surgery is the best solution, especially for the treatment of LBP [37]. Studies have found that even after anatomically successful surgery, 10 to 40% of the individuals continue to report pain complaints [38]. A subgroup of individuals undergoing surgery will also be unable to return to work after back surgery. Rates of postoperative return to work differ strongly and vary between 50 to 90% [39]. Recent studies reported that 82% of the individuals were able to return to work 3 months after back surgery [40, 41]. Also in Belgium, Du Bois and Donceel [42] found that 20% of the individuals were unable to resume work 1 year after a lumbar discectomy surgery. Although this considers only a minority of individuals with back pain and radicular pain, they represent a considerable burden to the society [13]. In those individuals, the complaints do not resolve despite anatomical successful surgery. Possible reasons are that psychological and social factors might overrule the effects of surgery, or the specific type of surgery might not have been the right solution for that particular spinal pathology. However, the mechanisms underlying the transition from acute to chronic pain remain poorly understood.

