### Sample size

Because there are no previous studies available on the prediction of pain severity and work resumption after back surgery that include all variables in our study, an a priori power analysis for multiple linear regression was conducted. This analysis revealed that, in a model with 12 predictors and a numerator degree of freedom of 14, with a power of 90% (an increase of 0.13 in R^2^), a total sample size of n = 167 is needed to detect a medium effect (effect size f^2^ = 0.1494) at an alpha level of 0.05. Considering potential dropouts from follow-up measurements (conservatively estimated at 50%), the aim for inclusion is set at 300 participants. Power calculations were performed in G*Power version 3.0.10.

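### Time to work resumption is right-censored at 12 months, so the multiple linear regression planned for it under the primary objectives should be replaced by a censored-data model

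*Protocol article*

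**What the plan says.** The Primary objectives part of the statistical analysis plan lists several analyses of the same process. Logistic regressions of return to work come first, at 6 weeks and at 3, 6 and 12 months. Then: "Next, a time-dependent Cox regression will be performed to examine the effect of the predictor variables on return to work over time". Both are repeated for sustainable resumption. After that: "Multiple linear regression analyses will be carried out to examine the effect of the predictor variables on the duration to resume work over time". Finally: "Log-rank test and Kaplan–Meier plots will be applied to compare rates of work resumption between participants with different profiles".

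No rule is given for entering a participant with no resumption date into the linear regression, and no analysis is named as the principal one. The opening paragraph of the statistical analysis plan commits to analysing all included participants and to choosing the method by the type of dependent variable.

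Follow-up ends 1 year after surgery (Design). The Back surgery section reports that in a Belgian study "20% of the individuals were unable to resume work 1 year after a lumbar discectomy surgery", and more widely: "Rates of postoperative return to work differ strongly and vary between 50 to 90" percent. On attrition the Sample size section says: "Considering potential dropouts from follow-up measurements (conservatively estimated at 50%), the aim for inclusion is set at 300 participants".

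**The concern.** Time to resumption is right-censored. For a participant still off work at month 12 we know only that the time exceeds 12 months. For one who leaves earlier without having resumed, we know only that it exceeds the time of last contact. Ordinary linear regression cannot use that information. It can drop these people, which selects the sample on the outcome, or it can enter a made-up value such as 12 months. Either choice cuts off the long end of the distribution, which is where the study hypothesis expects fear and avoidance to act.

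The loss may also be concentrated. The Demographic variables section cites a study in which 70% of people incapacitated for more than 3 months before surgery had not resumed at 1 year. Participants may enter with up to a year of sick leave, and duration of incapacity is a covariate in this model. If that rate applied here, a resumers-only regression would exclude most of that subgroup.

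At stake is a primary-objective estimate that understates the predictors' effect on time to resumption and stands beside a Cox estimate, with nothing to say which is to be believed.

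**Working it through.** The plan gives no figure for this bias, so there is none to reproduce. The fraction not resumed comes from the protocol. The distribution, spread and effect sizes are assumptions, because the protocol gives none.

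**Inputs.** Not resumed at 12 months, q: 20% (Belgian study), range 100 − 90 = 10% to 100 − 50 = 50%. Planned enrolment: 300. Follow-up: 12 months.

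**Participants with an observed duration, no dropout.** 300 × (1 − q) gives 240 at q = 20%, 270 at 10% and 150 at 50%.

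**Bias from the 12-month cut-off, no dropout.** Let log T = μ + b·x + s·e, with x and e standard normal, so ρ² = b²/(b² + s²). Let a be the standard normal (1 − q) quantile and λ = φ(a)/(1 − q). The variance of log T among resumers, relative to its full variance, is θ = 1 − aλ − λ².

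- Non-resumers dropped: slope ratio = θ / [1 − ρ²(1 − θ)].
- Non-resumers entered at 12 months: slope ratio = 1 − q.

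With b = 0.4 and s = 1.3, ρ² = 0.16/(0.16 + 1.69) = 0.0865:

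| q | a | λ | θ | Dropped | Entered at 12 months |
|---|---|---|---|---|---|
| 10% | 1.282 | 0.195 | 0.712 | 0.712/(1 − 0.0865 × 0.288) = 0.73 | 0.90 |
| 20% | 0.842 | 0.350 | 0.583 | 0.583/(1 − 0.0865 × 0.417) = 0.60 | 0.80 |
| 50% | 0 | 0.798 | 0.363 | 0.363/(1 − 0.0865 × 0.637) = 0.38 | 0.50 |

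Simulation agrees. At q = 20%, with b of 0.2 or 0.4 and s of 0.7 or 1.0, the resumers-only ratio was 0.59 to 0.65 and the 12-month ratio 0.80. With exponential times the resumers-only ratio was lower, 0.44 to 0.48.

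**Adding 50% dropout, spread evenly over the year (q = 20%).**

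- Dropout unrelated to the predictor: about 182 to 198 of 300 have an observed duration. The resumers-only ratio is 0.59 to 0.66 (log-normal) or 0.41 to 0.46 (exponential).
- Dropout related to the predictor (log-odds of ±1 per SD): the resumers-only ratio runs from about −0.05 to 0.91. With the censoring time used as if it were the outcome, it runs from 0.01 to 1.18. The last value exceeds 1, so the direction is not fixed.

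**Cox on the same kind of data (exponential times, q = 20%).** A true hazard ratio of 0.70 per SD was estimated at 0.695 to 0.699, and 0.85 at 0.846 to 0.850, with or without the 50% dropout. In these runs dropout depended at most on the predictor in the model. Dropout that depends on unmeasured prognosis was not tested.

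**The case against.** The strongest reply is that the right analysis is already planned. Visit-wise logistic regressions, Cox regression and Kaplan–Meier curves stand in the same section, and non-resumers count in all of them. The primary hypothesis also concerns sustainable resumption, which the protocol defines as dichotomous, so the linear regression is supplementary. This stands, and it limits the severity. A reader might infer that non-resumers are lost to the study; they are lost to this one model only. It does not remove the defect, because the regression is listed under the primary objectives with no order of precedence.

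Three other inferences go too far:

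- **Half the sample will be missing.** The 50% is a conservative planning allowance for missed follow-up measurements. Some who drop out will already have reported a resumption date.
- **The estimate is always pulled toward no effect.** That follows for the 12-month cut-off under the two handlings above. With predictor-related dropout it depends on who leaves and on a handling rule that is not stated.
- **The result must contradict Cox, or costs much power.** Attenuation need not change sign or conclusion. In an assumed setting (n = 150, log-SD 1.3, 20% not resumed, effect 0.3 per SD), entering non-resumers at 12 months gave 72–74% power against 71% for Cox.

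A handling rule might also sit in an unseen analysis plan. No such rule makes ordinary least squares suitable for a censored duration, and the article itself names the method.

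Finally, the variable is unclear. The Outcome variables section lists a continuous duration of work resumption and a time to relapse, but no duration until resumption. If time spent at work was meant, that too is cut off at 12 months.

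**Conclusion.** The concern holds for this one model. A right-censored duration has been assigned to ordinary linear regression, with no rule for participants whose duration is unobserved. With 20% not resumed, log-normal times and no dropout, the log-time slope is about 60% of its true value if non-resumers are dropped and 80% if they are entered at 12 months. Over the protocol's 10% to 50% range this becomes about 73% to 38%, and 90% to 50%. These sizes rest on the assumed distribution and effects. That the 12-month cut-off attenuates under either handling held in every no-dropout setting tried. Under predictor-related dropout, neither size nor direction can be stated.

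The documents do not support a claim that the primary question goes unanswered, since valid analyses of it are planned alongside. Severity: should-fix.

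**What to change.** Remove the linear regression of duration to resumption. Analyse time from surgery to work resumption with the planned Cox model, and state that participants who have not resumed are censored at last contact or at 12 months, whichever is earlier. If an effect on the duration scale is wanted, use an accelerated failure time model (log-normal or Weibull) with the same censoring. Should the sentence refer instead to the duration of work resumption listed under Outcome variables, say so and apply a censored-data model to that outcome.

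The cost is a change of wording. Dates of incapacity and of resumption are already to be collected, and the models are in standard software.
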